### Economic Evaluation

A cost-utility analysis will be undertaken from a societal perspective. Direct costs (product cost, training, distribution, and support) and indirect costs (time lost by participants and facilitators, perceived burden) will be collected using structured costing proformas completed by the study team and, for indirect costs, by participants via a tracking diary. Health-related quality of life will be assessed using the EQ-5D-Y, a generic, 5-dimensional health status measure developed specifically for use in children and adolescents [28]. The EQ-5D-Y has demonstrated acceptable feasibility, test-retest reliability (agreement 70%‐99% across dimensions), and known-groups validity in multinational pediatric and adolescent samples [29]. Reliability and content-validity data specific to Indian adolescents remain limited; a recent Indian study piloting the EQ-5D-Y-3L among school-going adolescents reported generally good feasibility but noted comprehension difficulty with the “having pain or discomfort” item and the “today” time-frame among some participants [30]. In light of this, the study team will conduct cognitive debriefing of the Hindi or Bengali translations of the EQ-5D-Y with a small sample of adolescent girls (n=10 per site) before baseline administration, and any comprehension difficulties encountered will be reported alongside the health-related quality of life findings. The EQ-5D-Y will be administered at baseline, 6 months, and 12 months. The incremental cost-effectiveness ratio will be calculated for MCs and MPs relative to usual practice (continued use of disposable pads) in terms of cost per quality-adjusted life-year gained, and results will be presented separately for each site to reflect potential differences in local costs.

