**Methods:**

This is a mixed methods, 2-phase interventional feasibility study at 2 Indian sites (Kalyani, West Bengal, and Chandigarh and Panchkula, North India), chosen to represent contrasting urban-planned and mixed urban-rural catchments. Phase 1 trains 40 community health and education workers (accredited social health activists, auxiliary nurse midwives, Anganwadi workers, and female teachers), who then deliver structured education to 912 adolescent girls in phase 2. A subset of 406 girls will be allocated to MCs or MPs and followed for 12 months via diaries, home visits, and focus group discussions. Quantitative data will be analyzed in SPSS; qualitative data will undergo reflexive thematic analysis in NVivo, guided by the Behavior Change Wheel and Capability, Opportunity, Motivation–Behavior framework. A cost-utility analysis using EQ-5D-Y and quality-adjusted life-years will assess cost-effectiveness from a societal perspective.

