### Phase 3: Intervention and Follow-up

A total of 416 adolescent girls aged 13‐19 years, equally divided between the 2 study sites, who complete the phase 2 sensitization and provide consent or assent for product use, will be allocated to either of the following:

MC group: receives a size-appropriate medical-grade silicone MC with instructional manual.MP group: receives 3 reusable MPs with instructional pamphlets.

Allocation to the MC or MP group will be based on participant preference following a structured counselling session in which both products, their insertion or use requirements, and maintenance needs are explained; girls who express no strong preference will be allocated using a randomization sequence generated in blocks of 4, stratified by site, to achieve approximately equal group sizes. This preference-informed allocation approach was chosen, rather than full randomization, because acceptability and correct use of MCs in particular are strongly influenced by willingness to use an internally inserted product, and forcing product allocation against strong preference was judged likely to compromise both retention and the validity of acceptability outcomes in a feasibility study of this nature; this deviation from a purely randomized design, and its rationale, is reported here transparently as recommended for feasibility study reporting [20].

Participants will receive free products along with instructional materials and menstrual-tracking diaries that record menstruation dates, school attendance, side effects, and usage challenges. Monthly follow-ups will occur through home visits at 1, 2, 3, 6, 9, and 12 months, conducted by trained community health and education workers using a structured follow-up checklist.

A 12-month follow-up duration was chosen in line with prior longitudinal descriptive work showing that adaptability and correct use of MCs typically stabilize only after several menstrual cycles of sustained use and support [25].

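### The cost-per-QALY ratio against continued disposable pads has no concurrently observed comparator and no stated source for one

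*Protocol article*

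**What the plan says.** The Economic Evaluation section plans a cost-utility analysis from a societal perspective, reported by site. The ratio is to be calculated for both products "relative to usual practice (continued use of disposable pads) in terms of cost per quality-adjusted life-year gained". The utility schedule is: "The EQ-5D-Y will be administered at baseline, 6 months, and 12 months". The cost items are "Direct costs (product cost, training, distribution, and support") and "indirect costs (time lost by participants and facilitators, perceived burden"). Indirect costs come from participants through a tracking diary.

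Under Phase 3: Intervention and Follow-up, girls who consent "will be allocated to either of the following", and two groups are listed: "MC group: receives a size-appropriate medical-grade silicone MC with instructional manual" and "MP group: receives 3 reusable MPs with instructional pamphlets". The abstract agrees: "A subset of 406 girls will be allocated to MCs or MPs and followed for 12 months via diaries, home visits, and focus group discussions". The Results section reports allocation to these two groups only (104 and 106 girls at March 2026).

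**The concern.** An incremental ratio needs two differences, one in cost and one in QALYs, each taken against the named comparator. The article fixes the comparator (continued pads) and fixes the groups followed (cups and panties), and the two do not match. A more detailed plan could name a substitute for the missing side, but it could not produce concurrent 12-month outcomes from girls who are not followed.

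Economic evaluation is the fourth of four objectives, and the abstract's conclusions offer cost-effectiveness evidence as a basis for scale-up. If the ratio is reported as worded, readers will take it for a controlled estimate, whereas the comparator side will have been assumed.

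**Working it through.** The section states no cost, utility, QALY or ratio, so there is no figure to reproduce. The check is a count of who is followed, then an illustration of sensitivity.

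**Who supplies comparator data**
- Groups with 6- and 12-month contacts: cups and panties (Phase 3 section, abstract, Results).
- Girls followed by design on disposable pads: 0.
- Sensitized girls planned to stay outside phase 3: 912 - 416 = 496, or 912 - 406 = 506 with the abstract's figure. The Phase 2 section gives them questionnaires on knowledge, attitudes and readiness before and after the sessions. It describes no EQ-5D-Y, cost collection or 12-month contact for them.
- Diaries, the source of indirect costs, are described only for girls who receive a free product.
- External dataset, decision model or carried-forward baseline for the pad comparator: none stated.

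**What the baseline can stand for**
- The article does not say that the baseline EQ-5D-Y precedes product use.
- The eligibility criteria (Textbox 1) do not require current pad use.
- The sample size section assumes that 5% already use sustainable products, and the Background section cites 64% hygienic protection nationally at ages 15-19. Neither figure measures pad use in this cohort, but baseline cannot be assumed to be uniformly pad use.

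**Illustration 1 (all utilities and the cost are assumed)**

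The QALY over one year, by area under the curve, is 0.25 × u0 + 0.5 × u6 + 0.25 × u12.
- Product group at 0.90, 0.92, 0.93: 0.225 + 0.460 + 0.2325 = 0.9175.
- Pad users starting at 0.90 with linear drift d over 12 months: 0.90 + 0.5 × (d/2) + 0.25 × d = 0.90 + 0.5d.
- QALY gain = 0.0175 - 0.5d. With an assumed extra cost of 1,000 units, the ratio is 1,000 / gain.

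| Drift d | QALY gain | Ratio |
|---|---|---|
| -0.02 | 0.0275 | 36,364 |
| 0 | 0.0175 | 57,143 |
| +0.02 | 0.0075 | 133,333 |
| +0.03 | 0.0025 | 400,000 |
| +0.04 | -0.0025 | sign reversed |

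The gain is zero at d = 0.0175 / 0.5 = 0.035. Carrying baseline forward amounts to assuming d = 0.

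**Illustration 2 (also assumed)**

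A utility gain of 0.05 on 5 of 28 days gives 0.05 × 5/28 = 0.0089 QALY per year. Linear drift of 0.02 is worth 0.02/2 = 0.010 QALY, more than that gain. Drift of 0.01 is worth 0.005, or 0.005/0.0089 = 56% of it. Whether drift swamps the effect depends on the values chosen. That drift enters the result directly does not.

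**The case against.** The strongest reply is that a comparator in an economic evaluation need not be a study arm. Pad costs can come from local prices or recall, and utilities from a model or from the baseline EQ-5D-Y. A condensed article may leave such sources to a health-economic plan that is not shown. This stands against a stronger reading, that data on usual practice cannot exist at all. The documents do not support that reading, because a baseline EQ-5D-Y is scheduled and pad prices are obtainable. It does not remove the mismatch: each substitute supports a weaker claim than the one printed, and the article names none.

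Three other inferences go too far.
- **Pad costs.** A reader might conclude that they will not be collected. Product cost is not restricted to cups and panties, and the costing proformas are not shown. All that can be said is that pad spending is not named.
- **Perceived burden.** A reader might infer that costing it double counts what EQ-5D-Y already values. The article does not define the term, and it may mean workload or inconvenience, so double counting is not shown.
- **Cup versus panties.** A reader might take this as a clean replacement comparison. Allocation follows preference, with randomization only for girls without a strong one, and Strengths and Limitations concedes possible selection differences. Adjustment does not remove preference-driven selection, and the comparison does not answer the usual-practice question.

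Girls who abandon their product and return to pads cannot fill the gap either, because they are selected by discontinuation.

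**Conclusion.** The concern holds in this form: the stated ratio against continued pads has no concurrently observed comparator and no named source, and the only contrast with usual practice inside the study is uncontrolled before-after. That finding rests on the article's text and on no assumption about utilities. The size does rest on assumptions. In the first illustration, drift from -0.02 to +0.03 moves the ratio about elevenfold (400,000 / 36,364 = 11), and +0.04 reverses the sign of the gain. These figures show sensitivity and do not predict the result.

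A reader might infer that this undermines the study as a whole. It does not. This is a feasibility study whose primary outcomes are usage, continuation, comfort and acceptability, and none of them depends on the pad comparator. The point limits what the fourth objective can conclude and should be corrected before analysis.

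**What to change.** 1. In Economic Evaluation, restate the usual-practice ratio as an exploratory before-after (or modelled) scenario. Specify that the baseline EQ-5D-Y is taken before product use and carried forward as the comparator utility.
2. Prespecify a sensitivity analysis over assumed background utility drift, for example -0.02 to +0.04 over 12 months, and state that the range is an assumption.
3. At baseline, record usual product, pad spending and time cost for girls still to be enrolled (416 - 210 = 206 at March 2026, or 196 with the abstract's 406). For the 210 already allocated, use recall or local prices and say so.
4. Report cups versus panties as an additional within-study comparison, adjusted for baseline EQ-5D-Y, site, age and allocation mode, and labelled non-randomized and subject to preference selection.
5. Add the lack of a concurrent usual-practice group to Strengths and Limitations, which now mentions only the non-random product allocation.

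The cost is a weaker stated claim, a few extra cost items, and recall error for the girls already enrolled. A new concurrent pad cohort is not proposed: it would need additional data collection, and girls starting after March 2026 could not reach 12 months by the planned end of follow-up in December 2026.

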### Ethical Considerations

#### Ethics Approval

The study protocol has been reviewed and approved by the Institutional Ethics Committee (IEC) of the Postgraduate Institute of Medical Education and Research, Chandigarh (application and approval reference number: IEC-I012024-3219; approved January 2024), and by the Institutional Ethics Committee of the All India Institute of Medical Sciences (AIIMS), Kalyani (application and approval reference or certificate number: IEC/AIIMS/Kalyani/certificate/2024/321; approved April 2024). Both reference numbers serve as the unique application and approval identifiers issued by the respective committees; no separate protocol registration number has been issued.

#### Participants’ Consent

Written informed consent will be obtained from all participants aged 18 years and above. For those under 18 years, written assent will be sought, in addition to consent from a parent or legal guardian, prior to participation. Participants will be informed that participation is voluntary and that they may withdraw at any stage without consequence. All data will be handled in accordance with strict confidentiality and data protection protocols. All identifiable information will be anonymized, and only deidentified data will be used for analysis and publication.

### Dissemination Plans

Findings will be disseminated via peer-reviewed journals, national and international conference presentations, and policy briefs for distribution to public health authorities and relevant stakeholders. Community-level dissemination sessions will also be organized to return results to participants and local decision-makers. Collaborations with educational institutions, health care providers, and policymakers will be sought to incorporate the project’s findings into existing menstrual health initiatives. A plan will also be developed to address any identified challenges in the adoption of sustainable menstrual products, aiming for broader acceptance and use.

## Results

This protocol reports on a study that is funded and currently being implemented. The study was funded by the Indian Council of Medical Research in March 2024 (Proposal ID: IIRPSG-2024-01-03552). Ethics approval was granted by the Postgraduate Institute of Medical Education and Research Chandigarh Institutional Ethics Committee in January 2024 and by the AIIMS Kalyani Institutional Ethics Committee in April 2024.

Phase 1 stakeholder sensitization workshops were completed at both sites between July and September 2024. All 40 targeted community health and education workers (20 per site) were enrolled and completed training, giving a phase 1 retention rate of 100%. Pre-post assessment of this cohort showed an increase in mean knowledge scores following training; a full analysis of these phase 1 outcomes will be reported separately once phase 2 data collection is complete, consistent with journal guidance to avoid reporting substantive analytic results at the protocol stage.

Phase 2 adolescent sensitization commenced in October 2024. As of March 2026, 512 of the planned 912 (56%; n=268 in Kalyani and n=244 in Chandigarh-Panchkula) adolescent girls have completed baseline sensitization sessions. Of these, 210 of the planned 416 (51%) girls eligible for phase 3 have provided consent or assent and have been allocated to the MC (n=104) or MP (n=106) group; enrollment in the remaining clusters is scheduled to continue through 2026.

One deviation from the original grant proposal has occurred to date: the Chandigarh site catchment was expanded to include the district of Panchkula, Haryana, in addition to the originally proposed urban Chandigarh sectors, in order to incorporate a peri-urban or rural comparison population within the same site, as detailed in the Study Setting section above. This change was approved by both ethics committees as a minor protocol amendment prior to the start of phase 2 recruitment at that site.

Data collection for phase 3 follow-up is expected to continue through December 2026. Data analysis is planned for the first quarter of 2027, with submission of substantive outcome findings for peer-reviewed publication anticipated by late 2027.

## Discussion

### Implications and Expected Findings

Despite growing awareness of the health, financial, and environmental benefits of reusable menstrual products such as MCs and MPs, their adoption in India has remained relatively low [1,9]. Our 2-phase, community-based model specifically empowers trusted frontline workers (ASHAs, ANMs, AWWs, and teachers) to provide adolescents with peer support and consistent education, thereby directly addressing barriers, such as cultural taboos, misinformation, and a lack of safe-use guidance, in line with the Capability-Opportunity-Motivation pathways specified in our theoretical framework [18].

There is evidence that peer-led and structured educational interventions substantially increase MC uptake. In a pilot study undertaken in Kerala, 50% of participants reported willingness to use an MC after receiving structured awareness education, and a study conducted in Nepal found that adolescents who received structured counseling were 60% more likely to accept the product [1,13,14]. Furthermore, despite being noninvasive and appealing to teenagers, reusable products such as MPs remain underused; for example, in a study conducted in Australia, only 24% of respondents reported using period underwear during their last menstrual period, and despite generally positive experiences, challenges such as limited information, upfront cost, and cleaning requirements were reported to hinder wider adoption [11].

The mixed methods design of this study allows triangulation of quantitative outcomes (eg, adoption rates, differences between MC and MP users) with qualitative insights into usability, stigma reduction, and cultural acceptability, using the prespecified joint-display and triangulation-protocol approach described above [19]. The inclusion of cost-utility analysis will provide data on affordability and scalability, aspects often missing from previous interventions [31]. If found to be feasible and acceptable at both sites, the intervention model has potential for scale-up through existing public health and school systems, contributing to menstrual equity, environmental sustainability, and the empowerment of adolescent girls.

### Strengths and Limitations

To our knowledge, this is the first study in India to evaluate both MCs and MPs through a community-driven, adolescent-focused intervention. It adopts a robust mixed methods design that integrates facilitator involvement, an explicit behavior-change theoretical framework, and a cost-effectiveness evaluation, with a prespecified approach to qualitative rigor and mixed methods integration. The engagement of grassroots health workers and educators enhances the contextual relevance and community reach of the study, and the inclusion of both urban and rural or peri-urban catchments at each site strengthens generalizability relative to earlier single-context studies. However, potential limitations include cultural resistance to product use, the risk of participant attrition over the 12-month follow-up period, the use of preference-informed rather than fully randomized product allocation (which may introduce selection differences between MC and MP groups), and limited generalizability beyond the 2 geographic sites studied.
